# DIALOR (DIgitAL cOaching for fRailty): protocol for a single-arm mixed-methods feasibility study of a digital health coaching intervention for older people with frailty in primary care

**DOI:** 10.1136/bmjopen-2023-080480

**Published:** 2024-05-16

**Keywords:** aging, health informatics, chronic disease, primary health care, frailty

## Abstract

**Background:**

Multidomain interventions in older adults offer the best opportunity to prevent, delay or reverse existing symptoms in the earlier stages of frailty and improve independence but can be costly, and difficult to deliver at scale. However, digital health interventions enable personalised care and empowerment through self-management of long-term conditions, used at any time and when combined with health coaching offer the potential to enhance well-being and facilitate the achievement of health-related goals. We aim to evaluate the feasibility and acceptability of a digital health platform for long-term disease management combined with health coaching for people living with mild-moderate frailty, targeting self-identified goals—activity, nutrition, mood, enhancing social engagement and well-being.

**Methods and analysis:**

This is a non-randomised feasibility, single-group, pretest/post-test study, using qualitative and quantitative methods. The digital health coaching intervention (DIALOR—DIgitAL cOaching for fRailty) has been developed for implementation to older adults, aged 65 years or older with mild to moderate frailty and diagnosis of one or more long-term health conditions in the community. Participants will receive 12 weeks of health coaching and have access to a mobile health platform for 6 months. The primary outcome measure is the acceptability and feasibility of DIALOR along with a range of secondary outcome measures (including frailty, functioning measures, quality of life, social engagement, diet quality and self-reported indicators) collected at baseline and at 6 months. The findings will inform whether a wider effectiveness trial is feasible and if so, how it should be designed.

**Ethics and dissemination:**

Ethical approval has been granted by the Southeast Scotland Research Ethics Committee 02 (reference: 22/SS/0064). Research findings will be disseminated in a range of different ways to engage different audiences, including publishing in open-access peer-reviewed journals, conference presentations, social media, dissemination workshop with patients, carers, and healthcare professionals and on institution websites.

STRENGTHS AND LIMITATIONS OF THIS STUDYA strength of the study design is using a mixed-methods approach with a qualitative understanding of the implementation process and quantitative measures to assess the effects on health outcomes and whether the trial is feasible.There is strong involvement of stakeholders and people with the lived experience to develop and guide the study.Potential limitations are as a feasibility study, it will assess a pretest and post-test intervention with non-randomisation of sample and to sufficiently engage hard-to-reach target groups including those with poor digital literacy and low socioeconomic status, impacting representation of the participant group and generalisability of the findings.

## Introduction

Frailty is a multidimensional syndrome characterised by cumulative loss of reserves and accumulation of deficits (eg, energy, physical ability, cognition, social and psychological aspects) that give rise to vulnerability and risk of adverse outcomes with advancing age.^1^ It is not an inevitable consequence of ageing but older adults with frailty have an increased risk of poor health, including falls, fractures and functional impairment, hospitalisation, need for nursing home care, and increased mortality.^2^ Older people with frailty experience impairment in their activities of daily living and often report a significant reduction in their quality of life.^3^ Furthermore, studies have shown that frailty may be related to decreased mood^4^ and may be shaped by social factors such as different levels of social support or living alone.^5^ Frailty affects about 12% of people aged ≥65 years worldwide^6^ and 14% of older people in the UK,^7^ and even higher numbers of individuals in the early stages of frailty, ranging from 19% to 53%.^8^ Frailty is an ever-present burden among international populations, which has been exacerbated by the impact of the COVID-19 pandemic^9^ and the resultant deconditioning.^10^

While moderate to severe frailty has a higher risk of physical health declines, mild to moderate frailty with some loss of physiological reserve is considered to be potentially reversible^11^ to a robust or stable state.^12^ Mild frailty is conceptualised as an intermediate stage on the Rockwood Clinical Frailty Scale,^13^ whereby older people experience some loss of physiological reserves but can usually recover after a negative stressor event, such as an infection or fall. This would indicate that interventions targeting earlier stages of frailty are more likely to reverse frailty decline. Moreover, there is evidence to suggest that interventions, particularly multidomain interventions in older adults including mobility, strength, balance, nutrition, physical activity and social support offer the best opportunity to prevent, delay or reverse existing symptoms of frailty and improve independence.^14–17^ Most multicomponent interventions incorporate involvement from a multidisciplinary team of health and social care professionals meaning they can be costly and difficult to deliver at scale.^18^

Digital health interventions (DHIs) enable personalised care and empowerment through self-management of a long-term condition (LTC), which can be used at any time, and may offer more cost-effective healthcare delivery.^19^ DHIs have been shown to be effective at achieving successful remote monitoring and management of chronic obstructive pulmonary disease (COPD) among older populations,^20^ suggesting that DHIs may be a feasible method of reaching remote communities. Studies show that digital approaches for lifestyle modifications in other LTCs such as type 2 diabetes, offer effective and scalable options when face-to-face or in-person programmes are not accessible or feasible, especially when offered with health coaching (HC).^21 22^

HC was originally described as the practice of health education and health promotion within a coaching context, to enhance the well-being of individuals and to facilitate the achievement of health-related goals.^23^ More recently, HC has been defined as helping people gain and use the knowledge, skills and confidence to become active participants in their care so that they can reach their self-identified health and well-being goals.^24^ In the last decade, HC has become increasingly embedded within integrated care services. However, the evidence base demonstrating the effectiveness of HC in the UK is limited. For example, a systematic review and meta-analysis assessing the impact of HC on type 2 diabetes found that HC was effective in achieving optimal glycaemic levels via self-management strategies.^25^ In the UK, health coaches working within primary care can be established clinical team members (eg, registered nurses, physician associates, physiotherapists, paramedics, occupational therapists and psychologists) or can be unlicensed health workers.^26^ Furthermore, research is emerging to show that HC may offer a promising approach to support effective lifestyle interventions for managing chronic conditions such as asthma, diabetes, cardiovascular disease (CVD) and mental illness on an international stage.^27^

Current integrated care systems in the UK have also implemented both DHIs via mHealth and HC to improve self-management of their LTCs, among older people living with COPD, diabetes and CVD.^28^ However, there remains a distinct lack of evidence, which demonstrates the effectiveness of HC for older adults who have at least two chronic conditions (multimorbidity), which is thought to affect up to 50% of older people (aged over 65 years).^29 30^ Further, the impact of HC for older adults with a diagnosis of frailty, is unknown, making a single disease-focused model of healthcare unsuitable to provide effective management.^31^ Therefore, targeted behaviour change interventions using DHIs such as mHealth, in conjunction with HC, have the potential to offer a proactive and wide-reaching approach to prevent frailty decline alongside the management of other diagnosed comorbidities and improve health and well-being outcomes.

This study aims to address this gap by codesigning and implementing a multicomponent intervention for people living with mild to moderate frailty. The DIgitAL cOaching for fRailty (DIALOR) intervention will include two key components (figure 1):

Digital HCThis will include digital HC sessions with a qualified health coach. An online platform (Zoom/Accurx/Microsoft Teams) will be used to deliver the digital HC intervention.Mobile health platformA suite of web-based platforms offering tailored clinical advice and support and self-management resources for the management of COPD, asthma, CVD and type 2 diabetes (details of the online platform can be accessed via https://mymhealth.com/). The platforms can be accessed by any electronic device (eg, smartphone, tablet or television) that has an active internet connection.

**Figure 1 F1:**
[figure not shown]
Overview of the DIALOR intervention and its functionalities. CARE, Congratulate, Ask, Reassure, Encourage; COPD, chronic obstructive pulmonary disease; DIALOR, DIgitAL cOaching for fRailty; LTC, long-term condition.

The primary objectives of this study are as follows:

Explore barriers and facilitators of the digital intervention from the perspectives of health coaches and healthcare professionals (HCPs) and determine the essential and desirable features of the intervention (wants and needs; preferred outcomes) to identify what functions will be most useful for the target population.Explore how HC can provide support for the management of mild to moderate frailty and LTCs from the perspectives of older people with mild to moderate frailty, carers, HCPs and health coaches.Determine the acceptability and feasibility of the intervention for older adults with mild/moderate frailty and another LTC referred to access HC services and willing to engage with the mobile health platform.

The secondary objectives of this study are as follows:

Explore the factors which inhibit or facilitate implementation including contextual factors, recruitment processes, resources needed, potential mechanisms and pathways to impact.Explore the acceptability and suitability of outcome measures (to inform sample size estimation and determine the primary outcome measure) for a future randomised controlled trial of the intervention (should it be feasible).Measure key domains for secondary outcome measures including participants who are able to self-report measures.

## Methods and analysis

### Intervention development

Over a 9-month period, intervention development will use guiding principles^32^ to inform codesign objectives of a logic model (figure 2) and ensure the intervention is acceptable, feasible, engaging and easy to implement. A systematic review and narrative synthesis will also guide the development of key features our intervention requires to meet user needs and best practice guidelines.

**Figure 2 F2:**
[figure not shown]
Proposed logic model. BMI, body mass index; EQ-5D-5L, EuroQol-5 dimensions-5 levels; FFQ, Food Frequency Questionnaire; IPAQ, International Physical Activity Questionnaire.

Behavioural analysis^33^ will triangulate evidence from (1) the narrative synthesis, (2) consultation with two stakeholder engagement groups (SEG) including HCPs, health coaches, commissioners of service and patients and (3) patient and public involvement (PPI) advisors and (4) a separate PPI group with lay advisors to identify barriers in each domain—activity/mobility, nutrition, social engagement and psychological well-being. Intervention components addressing each barrier will be theoretically mapped and characterised using the behaviour change wheel,^34^ the theoretical domains framework^35^ and normalisation process theory (NPT). NPT is the process through which complex, new ways of working become embedded into standard practice.^36^ We will use the Behaviour Change Techniques Taxonomy Version 1 (BCTT V.1)^37^ to code the behaviour change techniques delivering the identified intervention functions. This will provide a clear description of the intervention and factors which may influence its implementation and will be summarised in a behavioural analysis table. We will then convene another SEG meeting to discuss and refine the proposed logic model.

To identify challenges/enabling factors for delivery/implementation and intervention modifications needed to maximise engagement and behaviour change, we will conduct individual interviews with people with mild to moderate frailty (and their carers where appropriate) (n=20) and focus groups (n=4) with HCPs and health coaches (n=20) (figure 3). We will undertake purposive sampling to select older participants (following ethics protocol for consent), up to 20 semistructured interviews or until data saturation is reached, in accordance with robust methods in qualitative research.^38^ These will be conducted face to face, and audio recorded using dictaphones, otherwise, they will be conducted and recorded through Microsoft Teams or Zoom. Final in-house testing of the intervention will be undertaken before the commencement of the study. We will use the the Template for Intervention Description and Replication (TIDieR) checklist^39^ for intervention description which will report relevant outcomes to inform further planning for a future trial.

**Figure 3 F3:**
[figure not shown]
Process flow of study design. DIALOR, DIgitAL cOaching for fRailty; GP, general practitioner.

### Study design

This feasibility study is a non-randomised, single-group, pretest/post-test study, using qualitative and quantitative methods. This protocol was developed in accordance with the Standard Protocol Items: Recommendations for Intervention Trials reporting guidelines.^40^

This will be a mixed-methods prospective cohort study conducted within primary care settings in Southwest England. First, online group training on the intervention will be provided for health coaches by the research team, with top-up training and support as necessary throughout. A training manual will also incorporate frailty awareness and the Congratulate, Ask, Reassure, Encourage model approach.^41 42^ Intervention delivery will be tailored to each patient, with goals and strategies to help achieve them developed in conjunction with the health coach.

### Study setting

The study will work with GP practices in Primary Care Networks in Southwest England to identify patients already using the mobile health platform. GP practices will be eligible to take part if they are currently referring older people with mild to moderate frailty to access HC/social prescribing services and are willing to test new digital approaches.

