### Participant recruitment

Participant recruitment will be conducted within primary care services, at individual participating GP surgeries. Up to 50 older people with mild to moderate frailty will be recruited in line with previous sample size recommendations for feasibility studies.^43^ Eligibility criteria for older adults with mild to moderate frailty to participate in the study are outlined in box 1. The clinical care team from participating GP surgeries will identify eligible participants through existing medical records.

Box 1Inclusion and exclusion criteriaInclusion criteriaAged ≥65 years.Scoring as mild or moderately frail using the Electronic Frailty Index.Diagnosis of one or more long-term conditions including chronic obstructive pulmonary disease, type 2 diabetes, heart disease or asthma.Living in their own homes.Capacity to consent to participate.Able to communicate fluently enough in English to take part in the study.Able to recall their experiences sufficiently to engage with a health coach.Self-reported ability to use digital technology independently or with support.Exclusion criteriaNursing home resident or on the active waiting list for a place.Individuals who have a terminal illness and are being managed for end-of-life needs.Lacking the capacity to consent (eg, advanced dementia).

Three strategies will be used to recruit patients (1) via text message invitation to eligible patients which provides a link to a website with further information about the study, participant information sheet and contact information for the research team. Potential participants will be followed up by the research team to provide an opportunity to answer questions, confirm eligibility and obtain informed consent to participate, (2) by a member of the research team approaching eligible participants at the GP surgery, signposted by the clinical team and (3) via leaflets provided to eligible patients by the clinical team.

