### Digital support for patients

Patients with low digital literacy will be supported by the research team to access the digital HC and mobile health platforms. They will be offered a training manual, developed by the research team and coproduced alongside the SEG and PPI group alongside digital support leaflets and guidance on keeping safe online. To reduce the risk of digital inequity, internet-enabled tablets may be provided to individuals who lack a device, for the length of the study. Internet and data packages (via local council schemes) will be provided if the participant lacks access to an established internet connection. Digital support will be offered throughout the study via local council services (volunteer digital upskilling clinics embedded within public spaces, eg, GP surgeries and council libraries) and the research team.

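### Study setting describes finding existing platform users, which conflicts with the digital-support plan and matches neither the third primary objective nor Box 1

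*Protocol article*

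**What the plan says.** The protocol article describes the people to be studied in four places.

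- **Study setting:** practices in Primary Care Networks will be worked with "to identify patients already using the mobile health platform". The next sentence concerns practice eligibility: practices must be "currently referring older people with mild to moderate frailty to access HC/social prescribing services" and open to trying new digital approaches.
- **Third primary objective (end of the Introduction):** older adults with mild or moderate frailty and another long-term condition, "referred to access HC services and willing to engage with the mobile health platform".
- **Participant recruitment and Box 1:** "The clinical care team from participating GP surgeries will identify eligible participants through existing medical records". The only digital criterion is "Self-reported ability to use digital technology independently or with support". Platform use is neither an inclusion nor an exclusion criterion.
- **Digital support for patients:** "Patients with low digital literacy will be supported by the research team to access the digital HC and mobile health platforms". In addition, "internet-enabled tablets may be provided to individuals who lack a device, for the length of the study", and an internet package is offered to anyone without a connection.

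The platform is one of the two components of the intervention: under the abstract's Methods and analysis, participants get 12 weeks of coaching and "have access to a mobile health platform for 6 months". The design is single-group, pretest/post-test. The Secondary outcomes section labels baseline as preintervention for the self-reported indicators, and logins and time on the platform are collected at 6 months. Feasibility, part of the primary outcome, is judged on coaches trained, recruitment, retention, adherence and adverse events. Acceptability comes from interviews.

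**The concern.** The Study setting clause is a positive statement about which patients are sought, and it points to a different group from the one the rest of the article prepares for. Two practices following the same text could recruit different people: one from current platform users, the other from everyone in the records who meets Box 1.

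The difference bears on what the study can conclude. A current user has already been exposed to one of the two components before baseline, and there is no control group against which that exposure could be set. Such a person has also already taken the platform up, so their adherence to it says little about people meeting it for the first time. The results are meant to show whether a wider effectiveness trial is feasible and to inform its sample size and primary outcome measure, so an unclear population here would carry into that design.

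**Working it through.** The plan gives no figure to reproduce. The sample size, up to 50, rests on a cited recommendation and does not enter the argument. The check is a comparison of the text, followed by the algebra of the direction of bias.

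**1. The Study setting clause against each other section**

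- *Digital support:* direct conflict. The platform is web-based and needs a connected device. People without a device, a connection or the skills to gain access would hardly be current users, yet the article makes provision for them as participants.
- *Third primary objective:* mismatch. Willingness to engage looks forward and does not require present use. Existing users can satisfy it, so they form a subset of that population.
- *Recruitment and Box 1:* mismatch of the same kind. Patients are found in medical records, no list of platform users is mentioned, and existing users can qualify but need not be users to do so.

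**2. What follows if existing users are enrolled**

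- Baseline comes after exposure to the platform began, but still before the study's coaching. It is therefore not pre-intervention for the platform component or for the combined intervention.
- The pre-post change leaves out what the platform had already done. What remains reflects mainly the added coaching, together with any change that would have occurred anyway.
- A total of logins or time read off at 6 months could include use before enrolment unless counting starts at baseline.

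**3. Direction and possible size for adherence**

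Let w be the share of the sample already using the platform, a_N the adherence of new users, and a_N + d that of existing users. Then

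observed adherence = w(a_N + d) + (1 − w)a_N = a_N + w·d,

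so the observed rate exceeds the new-user rate by w·d. Neither w nor d is in the documents. Taking d = 10 to 30 percentage points as an assumption:

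- w = 0: 0 points
- w = 0.5: 0.5 × 10 = 5 to 0.5 × 30 = 15 points
- w = 1 (the Study setting clause read literally): 10 to 30 points

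The bias is upward only if d > 0. That is plausible, since these people have already adopted the platform, but the documents do not show it.

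**4. Which feasibility measures are touched**

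- Platform adherence and usage: likely higher.
- Retention and acceptability: possibly higher.
- Number of coaches trained: unaffected.
- Number recruited: could fall if the sample were confined to existing users.

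**The case against.** The strongest reply is that the Study setting clause does not govern enrolment. The operative text is the recruitment section, which searches medical records against Box 1 and does not mention platform use. The clause stands next to a sentence on practice eligibility and may be loose wording for practices where the platform is already on offer. On that reading w could be small or zero and nothing is biased. This stands as a limit on the consequences: they apply only as far as existing users are in fact enrolled. It does not remove the conflict, because the article nowhere says that the clause means practices rather than patients.

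Three stronger readings are tempting but not supported.

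- *Feasibility as a whole is inflated.* Platform uptake is not among the listed feasibility measures, the number of coaches trained is untouched, and recruitment could move the other way.
- *All the descriptions of the population are incompatible.* Only the Digital support section clashes directly. Even there, it is too absolute to say that someone without their own device cannot be a user, since carers are expected to use the platform too.
- *Prior coaching contaminates baseline in the same way.* Practices already refer to coaching or social prescribing, but nothing says that participants are already being coached, and the study's coaching comes from coaches given study-specific training. Earlier general coaching is not this intervention.

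It can also be said that the study is mainly descriptive and that the article already concedes limits in reaching people with poor digital literacy. That is true, but the concession does not cover selection of people who already use the platform.

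**Conclusion.** The point holds as an inconsistency about who is studied, with conditional consequences. The Study setting clause conflicts directly with the Digital support section and does not match the third primary objective or the recruitment section and Box 1. To the extent that existing users are enrolled, baseline is not pre-intervention for the platform, pre-post change reflects mainly the added coaching, and platform adherence and usage, possibly also retention and acceptability, are likely to exceed those in new users.

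Confidence is high for the conflict in wording, moderate for the direction of bias, and absent for its size. The 5 to 15 and 10 to 30 point ranges rest wholly on an assumed adherence difference and assumed shares of existing users. A reader might infer from the clause that every participant is an existing user and that the feasibility result is therefore overstated by a known amount. The documents support neither step.

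**What to change.** Reconcile the Study setting section, the third primary objective, the recruitment section with Box 1, and the Digital support section to one population, stating whether prior platform use is required, allowed or excluded. One way is to reword the Study setting clause so that it refers to practices where the platform is available, and to screen all patients who meet Box 1.

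If existing users remain eligible:

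- record prior platform use at baseline;
- count logins and time on the platform only from baseline;
- report adherence, usage and the pre-post description separately for existing and new users.

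There is no need to make people new to both the platform and coaching the main analysis group, which would add a restriction that the protocol does not contain.

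The cost is a reworded clause, one baseline item and one split of the tables. The new-user estimate will be less precise and probably less favourable. For example, if half of the maximum of 50 were new users, the 95% half-width for a proportion near 50% would go from 1.96 × √(0.25/50) = 0.139 to 1.96 × √(0.25/25) = 0.196, that is, from about 14 to about 20 percentage points.

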Self-reported indicators such as height, weight, body mass index, number of falls (per year), goal attainment, alcohol intake and smoking habits (if applicable) will be measured at baseline (preintervention), throughout the study during digital HC intervention and at 6 months (postintervention).

Data will be collected from the mobile health platform which will be recorded automatically by inbuilt tracking software, including usage patterns from the number of logins, and the length of time that older people and their carers use the platform. These data will be collected at 6 months for each patient participant (postintervention).

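### The protocol contradicts itself on whether participants already use the mobile health platform, so what its platform uptake and adherence results describe is left open

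*Protocol article*

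**What the plan says.** The passages that bear on who enters the study do not agree.

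- **Study setting.** The study will work with practices "to identify patients already using the mobile health platform". Nothing in that section limits this to a subgroup or to the development-phase interviews.
- **Introduction, primary objectives.** The target group is older adults with mild or moderate frailty and another long-term condition, "referred to access HC services and willing to engage with the mobile health platform".
- **Participant recruitment.** "The clinical care team from participating GP surgeries will identify eligible participants through existing medical records". The only digital criterion in Box 1 is "Self-reported ability to use digital technology independently or with support". Prior platform use is neither required nor excluded.
- **Digital support for patients.** "Patients with low digital literacy will be supported by the research team to access the digital HC and mobile health platforms". In addition, "internet-enabled tablets may be provided to individuals who lack a device, for the length of the study", and internet packages are offered to those without a connection.

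The Introduction names the platform as one of two intervention components, beside digital health coaching. The Abstract says: "Participants will receive 12 weeks of health coaching and have access to a mobile health platform for 6 months". Under Primary outcomes, feasibility is judged on, among other things, recruitment, retention and adherence. Under Secondary outcomes, the platform's tracking software supplies "usage patterns from the number of logins, and the length of time that older people and their carers use the platform", collected at 6 months, and the baseline assessment of the self-reported indicators is labelled as preceding the intervention.

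**The concern.** If the Study setting sentence is followed, participants have already taken up one of the two components before they enrol. Three results then change meaning for those people:

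- Platform adherence and usage are those of someone who has already adopted the platform.
- First uptake, a central feasibility question in older people with frailty, is not observed at all.
- The baseline measurement is taken with the platform already in place. Their 6-month change then reflects coaching added to the platform, whereas a new starter's change reflects coaching and platform together.

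If the other passages are followed, many participants may be new to the platform and these problems shrink or vanish. The article states that its findings will inform whether an effectiveness trial is feasible and how to design it. That reading requires knowing which population the platform results come from.

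**Working it through.** **Step 1: compare the passages.** The article states no figure on this point, so there is none to reproduce. The check is first one of text.

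| Place | Who is described | Prior platform use |
|---|---|---|
| Study setting | Patients found through practices | Already using it |
| Primary objectives | People referred for coaching | Prospective: willing to engage |
| Participant recruitment and Box 1 | Eligible patients found in records | Not mentioned |
| Digital support for patients | Includes people with no device or connection | Unlikely |

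The first row cannot describe the same population as the last: someone without a device or connection is unlikely to be a current user of a web-based platform. The middle rows admit both kinds of patient. The share of existing users, f, could therefore be anything from 0 to 1.

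**Step 2: which outcomes are exposed.** DIALOR has two components. Nothing in the article says platform users have already had DIALOR coaching. Platform uptake, platform adherence, platform usage and the platform-free status of the baseline are exposed. Coaching adherence and the coaching-naive baseline are not directly exposed.

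**Step 3: how large could the effect be?** This is illustration only. The adherence rates below are assumptions, and so is their direction (higher in existing users).

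Inputs: n = 50 (the maximum under Participant recruitment); pN = platform adherence in new starters; pE = platform adherence in existing users.

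Pooled adherence = f × pE + (1 − f) × pN. Excess over the new-starter rate = f × (pE − pN). 95% half-width = 1.96 × √(p(1 − p)/50), where p is the pooled value.

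| pN, pE | f | Pooled | Excess | Half-width at n=50 |
|---|---|---|---|---|
| 0.50, 0.80 | 0.5 | 0.65 | 0.15 | 0.132 |
| 0.50, 0.80 | 1 | 0.80 | 0.30 | 0.111 |
| 0.60, 0.80 | 0.5 | 0.70 | 0.10 | 0.127 |
| 0.60, 0.80 | 1 | 0.80 | 0.20 | 0.111 |
| 0.60, 0.70 | 0.5 | 0.65 | 0.05 | 0.132 |
| 0.60, 0.70 | 1 | 0.70 | 0.10 | 0.127 |

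Example, first row: 0.5 × 0.80 + 0.5 × 0.50 = 0.65; 0.65 − 0.50 = 0.15; 1.96 × √(0.65 × 0.35/50) = 0.132.

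With a wide gap the excess is larger than the sampling error. With a narrow gap it is smaller. At f = 0 it is zero. At f = 1 no participant informs first uptake, whatever the rates. A larger sample would narrow the interval but would not remove the excess.

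**Step 4: precision after separating the groups.** If half of 50 are new starters (n = 25) and their adherence is 0.60, the half-width is 1.96 × √(0.60 × 0.40/25) = 0.192, against 0.136 with all 50.

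**The case against.** The strongest reply is that the Study setting sentence is one clause in a paragraph about practices, while eligibility is defined in Box 1, which does not ask for prior use. All three recruitment routes go to eligible patients in general, and the support arrangements plainly expect some people with no device. This stands against the reading that the sample consists of established users. A reader might infer that from the Study setting sentence alone, but the rest of the article does not support it. It does not remove the contradiction, because that sentence is unqualified and would change the sample if followed.

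Other inferences also go further than the document allows:

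- **That existing users are not starting DIALOR.** They would still start the coaching component at enrolment.
- **That retention and acceptability are biased upward.** This is plausible but not shown. Retention is staying in a study that includes 12 weeks of coaching and a 6-month assessment, and acceptability comes from open-ended interviews that also include professionals and coaches.
- **That selection error exceeds sampling error.** This depends wholly on the assumed rates, and it reverses with the 60% and 70% pair.
- **That login totals include use before the study.** The 6-month access period reads naturally as the counting window, and a condensed article may leave the exact start to the full protocol. The same applies to a baseline variable for prior use. Neither absence is a finding in itself.
- **That existing users could not serve as controls in a later trial.** The article names no comparator for that trial.

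Finally, adding coaching for current platform users is a legitimate question. The Introduction notes that UK care systems already use both elements. The difficulty is that the article does not say which question it asks.

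**Conclusion.** The concern holds as an internal contradiction about the source population, which leaves the mix of new and existing platform users unfixed. For each existing user enrolled, first uptake is unobserved, platform adherence and usage reflect prior adoption, and the baseline does not precede the platform component. Because adherence belongs to the primary feasibility outcome, this limits what the study can conclude about platform uptake.

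The size cannot be determined from the article. The illustrative excess of 5 to 30 percentage points, for half or all participants being existing users, rests on assumed adherence rates and an assumed direction. The contradiction itself rests on no assumption.

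**What to change.** Reconcile Study setting with the primary objectives, Participant recruitment (Box 1) and Digital support for patients by stating whether prior platform use is required, allowed or excluded.

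If it is allowed:

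1. Take each participant's platform registration date from the tracking software.
2. Count logins and time from enrolment only.
3. Report platform uptake, adherence and usage separately for new and existing users, and show pre–post change by the same split, descriptively.
4. Base conclusions about platform uptake for a future trial on the new starters.

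The cost is a clarified sentence and one date field that the tracking software should hold. This remains possible after recruitment has begun. Restricting entry to unregistered patients would be a change of eligibility and is hardly practical now. Under Status the study runs from September 2023 to September 2024, so 6-month follow-up implies enrolment ending around March 2024, before the article appeared in May 2024.

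The downside is precision: at most 50 people are divided between two groups, intervals widen (for example from 0.136 to 0.192 in the illustration above), and the adherence figure for new starters may be less favourable than the pooled one.
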